#### Haemodynamics/inflammation subgroup

In a subgroup of 50 patients having surgery at US Linköping, additional haemodynamic measurements will be performed. On arrival at the anaesthesia department, an arterial line is placed and connected to a pulse-contour analysis device (Pulsioflex, Getinge, Gothenburg, Sweden). Mean arterial pressure, cardiac index, stroke volume index, heart rate, stroke volume variation, pulse pressure variation, systemic vascular resistance index, cardiac power index and dPmx (measure of contractility of the heart's left ventricle) are recorded and stored continuously 5 times per min. In addition, the above measurements are recorded manually on a separate sheet on arrival at the operating room, just before anaesthesia, before the start of surgery, 1 hour after the start of surgery, at the end of surgery, on arrival at the PACU and on discharge from the PACU.

In the same subgroup, blood is sampled for analysing the inflammatory and neuroendocrine response on the day of surgery before arriving in the OR, 1 hour after abdominal insufflation, 2 hours after the end of anaesthesia and on POD 1 and 3 (if not discharged). A study flow chart is shown in figure 1.

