### Outcome measures

Primary and secondary outcome measures of this study are shown in table 2 with additional details provided in online supplemental table 1. The primary outcome measure of this study is QoR-15 on POD 1. Our primary hypothesis is that the reduction in QoR-15 from baseline before surgery to POD 1 is at least 8 points less in the morphine spinal group compared with the control group treated with intravenous lidocaine.

**Table 2 T2:** Primary and secondary outcome measures

**1**	**QoR-15 score at POD 1 (primary outcome measure)**
2	QoR-15 score preoperatively
3	QoR-15 score at POD 7
4	Pain (NRS) at rest and during motion 2 hours after arrival to the PACU
5	Pain (NRS) on POD 1–3
6	Pain (NRS) at rest and during motion on POD 7
7	Time from arrival in the OR to start of surgery
8	Time from end of surgery until leaving the OR
9	Incidence of unplanned termination of the lidocaine infusion
10	Amount of remifentanil in patients given remifentanil
11	Amount of intraoperative opioids in patients not receiving remifentanil, expressed in morphine equivalents
12	Length of stay at the PACU/ICU/HDU
13	Amount of opioids administered at the PACU/ICU/HDU during the first 24 hours after end of surgery
14	PONV requiring treatment at 0–6 hours and 6–24 hours postoperatively as well as during the whole postoperative stay
15	‘Time out-of-bed’ on POD 1–3
16	Amount of opioids administered during the first 24 hours at the PACU/ICU/HDU and in the ward
17	First POD passing gases
18	First POD passing stool
19	Incidence of pruritus
20	Length of stay
21	DAOH30
22	Postoperative complications until POD 30
23	Requirement for opioids after discharge
24	Incidence of respiratory depression leading to the use of a μ-antagonist within 48 hours of induction of anaesthesia
25	Intraoperative fluid balance
26	Time with low blood pressure during anaesthesia
27	Lowest MAP within 10 min after induction of anaesthesia
28	Highest MAP within 10 min of start of abdominal insufflation
29	Fraction of patients needing norepinephrine within 15 min after start of abdominal insufflation
30	Fraction of patients needing norepinephrine intraoperatively (later than 15 min after start of abdominal insufflation)
31	Average infusion rate of norepinephrine, in patients receiving norepinephrine, before 15 min after start of abdominal insufflation
32	Average infusion rate of norepinephrine, in patients receiving norepinephrine, after 15 min after start of abdominal insufflation

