### Statistics

#### Calculation of sample size

In a previous feasibility study including 30 patients undergoing robot-assisted upper urinary tract surgery under general anaesthesia without morphine spinal or intravenous lidocaine, QoR-15 decreased from a median (IQR) preoperative value of 141 (128 – 145) to 106 (88–103) on POD 1 (means (SD) 136 (11) and 105 (22); unpublished data). We assume that variance ((SD)^2^) is 400 in both groups on POD 1. With an MCID of 8, a desired alpha value of <0.05 and a power of 80% 100 subjects are needed in each group (GPower V.3.1.9.7, Heinrich-Heine-Universität Düsseldorf, Germany). To compensate for dropouts, a total of 220 subjects will be included in the trial.

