#### Analysis groups

The primary outcome is analysed in the entire trial group according to the intention-to-treat (ITT) principle, except for the subjects who do not undergo the planned robot-assisted surgery within 12 months from inclusion, and/or neither receive intervention nor control treatment, and/or leave the trial and/or die before the POD 1 measurement. The clinical secondary analyses are also analysed in this entire trial group according to ITT. These analyses will be supplemented with:

A per protocol (PP) analysis of the primary hypothesis as well as NRS POD 1–3, where subjects who are included in the ITT analysis, however, without sufficient preoperative effect of the spinal analgesia, and/or where lidocaine infusion was prematurely terminated, and/or where the surgery was converted to an open procedure are excluded.An ITT and PP analysis as above where subjects with problematic pain are omitted. Problematic pain is defined here as preoperative opioid use for more than 1 month.

The haemodynamic and biochemical parameters are analysed only in the subgroup that is monitored with advanced haemodynamic monitoring according to the PP principle, that is, subjects with a spinal anaesthetic without adequate preoperative spread, and/or where lidocaine infusion was prematurely terminated, and/or where the surgery was converted to an open procedure are excluded.

Normal distribution will be tested with the Shapiro-Wilks test, except for QoR-15 and NRS data which are assumed to be not normally distributed. All significance tests are done two-sided. A p value lower than 0.05 is considered significant. No corrections for multiple comparisons are made unless otherwise specified.

Single missing values are in principle not imputed. In exceptional cases, if missing data cause an entire data series (in time) to be misleading, the missing data can be imputed with the average value of the two measurements closest in time, provided that this results in a reasonable value.

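### The subgroup-only, per-protocol rule for haemodynamic parameters names no outcome numbers and, read literally, takes in blood-pressure and norepinephrine outcomes (Table 2, items 26–32) that do not need the subgroup

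*Protocol article*

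**What the plan says.** The Analysis groups section of the protocol article sets two population rules for the secondary outcomes.

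- **Clinical outcomes:** "The clinical secondary analyses are also analysed in this entire trial group according to ITT".
- **Haemodynamic and biochemical outcomes:** "The haemodynamic and biochemical parameters are analysed only in the subgroup that is monitored with advanced haemodynamic monitoring". The per-protocol principle applies. Patients are excluded if the spinal did not spread adequately, if the lidocaine infusion was ended early, or if surgery was converted to open.

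Neither class is defined by item number. Table 2 gives no population for items 26–32, which are time with low blood pressure (26), lowest and highest MAP in set windows (27–28), norepinephrine need (29–30) and norepinephrine rate among recipients (31–32). Item 29, for example, reads "Fraction of patients needing norepinephrine within 15 min after start of abdominal insufflation".

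The Haemodynamics/inflammation subgroup section states: "In a subgroup of 50 patients having surgery at US Linköping, additional haemodynamic measurements will be performed". The planned total is given under Calculation of sample size: "To compensate for dropouts, a total of 220 subjects will be included in the trial".

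**The concern.** Items 26–32 are haemodynamic in content, so the plain wording places them in the subgroup. Unlike cardiac index or stroke volume variation, they do not depend on the pulse-contour device. Two things are at stake.

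**Precision and coverage.** Hypotension is one of the disadvantages of the spinal that the article names in the Introduction, under Ethics and in the Discussion. The Discussion also uses it to justify the stricter MCID of 8. Hypotension treated with norepinephrine alone is not a Box 1 safety outcome, because that box requires other vasoactive drugs or a transfer to a higher level of care. Box 2 keeps it out of adverse-event registration. Items 26–32 are therefore the main place in the article where ordinary intraoperative hypotension is compared. Under the subgroup rule that comparison rests on at most 50 patients from one hospital.

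**Bias.** The per-protocol exclusions are linked to the outcome itself. A control patient whose infusion is stopped for severe unexplained hypotension leaves the hypotension comparison.

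In addition, because the classes are undefined, the population for these seven items could be settled after results are seen, in a plan that tests secondary outcomes without multiplicity correction unless otherwise specified.

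**Working it through.** **1. Reproduce the plan's own figure.** Inputs from Calculation of sample size: "We assume that variance ((SD)^2^) is 400 in both groups on POD 1", so SD = 20; difference 8, two-sided alpha 0.05, power 80%.

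n per group = 2 × (1.960 + 0.842)² × 400 / 8² = 98.1, rounded up to 99. The t-test version gives 99.08, rounded up to 100. This matches the article: "a power of 80% 100 subjects are needed in each group". Going from 200 to 220 allows for 1 − 200/220 = 9.1% dropout. The whole-trial set is therefore 200 to 220 patients.

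**2. Share of patients left out by the subgroup rule.**
- Of 220: (220 − 50)/220 = 77.3%.
- Of 200: (200 − 50)/200 = 75.0%.
- If 10–20% of the subgroup is excluded per protocol (an assumption), 45 to 40 patients remain, and 80–82% of 220 are left out.

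**3. Precision, for items defined in all patients (26–30).** An even 25/25 split of the subgroup is assumed.
- SE ratio = √(220/50) = 2.10, or √(200/50) = 2.0 against 200 evaluable patients.
- 95% CI half-width for a difference in proportions near 50% (assumed) = 1.96 × √(2 × 0.25/n). This is ±28 points at n = 25 per arm and ±13 points at n = 110.
- Standardised difference detectable with 80% power (t-test): 0.81 at 25 per arm and 0.38 at 110 per arm.
- Power for an assumed norepinephrine need of 40% vs 60% (normal approximation, pooled variance under the null). At n = 25: (0.20 − 1.96 × 0.1414)/0.1386 = −0.56, power 29%. At n = 110: (0.20 − 1.96 × 0.0674)/0.0661 = 1.03, power 85%. For 50% vs 70%, the same method gives 30% and 86%.

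These figures do not apply to items 31–32, whose denominator is norepinephrine recipients and so is smaller under either rule.

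**4. Outcome-dependent exclusion.** Three statements are set side by side:
- Interventions and measurements: the infusion may end early for unexplained severe hypotension or severe arrhythmias.
- Ethics: the same stopping reasons are repeated.
- Analysis groups: patients with a prematurely ended infusion are excluded from the haemodynamic analysis.

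If x of n controls have the event and k of those x are stopped for it, the observed proportion falls from x/n to (x − k)/(n − k), which is lower whenever x < n. With 25 controls and 40% needing norepinephrine (assumed), x = 10, and one such exclusion moves the proportion from 10/25 = 40% to 9/24 = 37.5%. In the spinal arm the rule drops patients without adequate spread, who plausibly have less sympathetic block. Both exclusions push towards a larger apparent haemodynamic cost of the spinal. How often they occur is not given.

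**5. Can items 26–32 be obtained in all patients?** All subjects have basal monitoring, and haemodynamic treatment follows local routine (Interventions and measurements). Drug administration is routinely documented in the anaesthesia record (Protocol adherence), and trial data are transferred from that record to the CRF (Blinding). The subgroup measurements are described as additional, and norepinephrine is not among them. Together these make whole-trial analysis plausible, but no sentence says that these variables are collected for everyone.

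**The case against.** A reader might infer that the section contradicts itself, giving the same endpoint both an ITT population of 220 and a per-protocol population of 50. The text does not support that. The ITT rule covers only *clinical* secondary analyses, and no Table 2 item is assigned to both classes. The other pointers favour the subgroup: the Introduction says that haemodynamic effects are studied in a subgroup, and MAP heads the list of values recorded there, stored continuously. On that view the authors made a choice and the complaint is a design preference. A reader might also infer that data already in hand from 170 patients would be thrown away, which presumes collection that the article does not document.

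Further fair points:
- Online supplemental table 1, which is not shown, may assign items to populations.
- Items 31–32 were never measurable in every patient.
- Box 1 records the more severe hypotension without a subgroup restriction.
- These are 7 of 42 listed outcomes, and the primary analysis is untouched.

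All of this stands, and it removes any claim of contradiction. It does not answer the remaining point. If the literal reading is the intended one, it applies to these items a small single-centre set and an exclusion tied to the outcome, apparently without need. If it is not intended, the unqualified restriction in the main text is wrong as worded, whatever the supplement says. This goes beyond detail left to an analysis plan, because the article states the population rule itself.

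**Conclusion.** The point holds as a badly fixed analysis population, not as a contradiction. Taken literally, the rule analyses items 26–32 in at most 50 patients from one centre and leaves out 75–77% of the trial before per-protocol exclusions. The standard error is about 2.1 times larger for items 26–30. It also removes controls whose infusion was stopped for severe unexplained hypotension from the comparison of hypotension.

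The 50, 200 and 220 are the article's own figures. The power and interval figures rest on an even split and assumed event rates. Availability of the data in all patients is an inference from the monitoring and record-keeping passages. The size of the exclusion bias cannot be estimated from the article, and its likely direction is against the spinal. The primary outcome is not affected.

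**What to change.** In Analysis groups, define the two classes by Table 2 item number.

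- Limit the subgroup rule to outcomes that need the pulse-contour device or the study blood samples: items 33–40 and 42.
- State explicitly which set applies to item 41 (heart rate), which is listed with the subgroup recordings but does not need the device.
- Analyse items 26–32 in the entire trial group by ITT, with items 31–32 among norepinephrine recipients, and give the per-protocol analysis as supportive.
- Check that supplemental table 1 agrees.

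The cost is a sentence or two, plus a little more data extraction if blood pressure and norepinephrine are not already transferred to the CRF for all patients. Recruitment was at 54 patients on 1 October 2025 and the randomisation code is to be broken only when data acquisition is complete, so the sets can be fixed before anyone sees results for these outcomes by arm.

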### Inclusion and randomisation

Test subjects are included consecutively. Randomisation of the participating subjects takes place after inclusion in the trial, before the start of anaesthesia. For each participating hospital (apart from US Linköping, see the next section), Forum Östergötland prepares before the start of the trial 100 sequentially numbered, opaque and sealed envelopes in series of 20 with both groups distributed 1:1. For US Linköping, 200 envelopes are prepared in the same way. Forum Östergötland retains the randomisation codes.

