### Interventions and measurements

Baseline values for QoR-15 and pain Numeric Rating Scale (NRS) are collected before the day of surgery. On the day of surgery, preoperative preparations on the ward follow local routines. A standardised premedication with acetaminophen and ondansetron is recommended. On arrival in the operating room all subjects are provided with basal monitoring including Bispectral Index (BIS). Induction and maintenance of anaesthesia is performed primarily with propofol and remifentanil or sevoflurane and fentanyl. Intubation and ventilator settings are managed according to local routine. Propofol or sevoflurane administration is controlled primarily by BIS, while the administration of remifentanil or other opioids intraoperatively is governed primarily by subject haemodynamics.

Haemodynamic treatment with fluids and drugs is performed according to local routine. A dose of 0.07 mg/kg actual body weight (ABW) intravenous morphine is recommended 30–60 min before the planned awakening, as well as 1 mcg/kg ABW intravenous fentanyl at the termination of remifentanil infusion when used.

Subjects randomised to the intervention group receive preoperative spinal analgesia with 15±5 mg bupivacaine and 0.2–0.3 mg conservative-free morphine using a 24G or smaller spinal pencil-point needle. In case of difficult puncture and/or pronounced discomfort, the procedure is aborted, and the subject is treated with intravenous lidocaine similar to the control group.

In subjects randomised to the control group, an intravenous infusion of lidocaine is started as soon as possible after induction. A bolus dose of 2 mg/kg ideal body weight (IBW, corresponding to a body mass index (BMI) of 22 kg/m^2^) is given over 10 minutes. An infusion of 2 mg/kg/hour IBW is then started. In patients with a BMI <22, ABW is used for calculation of bolus and maintenance doses. The infusion is terminated at the end of surgery or earlier in the event of unexplained severe hypotension or severe arrhythmias.

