Due to the disadvantages of morphine spinal, it is clinically relevant to investigate whether morphine spinal is actually better than an alternative additional treatment without the disadvantages of morphine spinal. Of the possible strategies considered to have the potential to approach equivalent effect on postoperative recovery as a morphine spinal, only intravenous lidocaine is not associated with renal effects or a negative effect on tumour progression.

Lidocaine given intravenously perioperatively for pain relief is a so-called ‘off-label’ use, similar to many other drugs used in anaesthesia, for example, epidural fentanyl. The use of lidocaine in this way is currently limited in Sweden, but it is routine in many hospitals abroad and is recommended in various international guidelines.^24 25^ The bolus dose and infusion rate in the current trial are well in line with previous studies on the effect of lidocaine as a pain-relieving drug given intravenously.^13^

The lidocaine infusion will be started and finished while the subject is closely monitored in the operating room. Signs of systemic toxicity will thus be detected early and treatment rapidly initiated. The relatively short treatment time means that the risk of accumulation and late toxicity is considered negligible, even in subjects with pre-existing or new-onset renal failure. The infusion is stopped prematurely if severe unexplained hypotension or arrhythmia occurs. Patients with severe kidney or liver failure or advanced heart disease will not be included in the trial. The use of larger doses of local anaesthetic in other ways during the primary operation is not permitted in those receiving lidocaine.

The trial involves the handling of sensitive personal data. The risk of various forms of privacy infringement is minimised through informed consent and pseudonymised processing and storage of research data, including sample material.

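### The advanced haemodynamic and biochemical outcomes (33–42) have only a per-protocol analysis, which drops lidocaine patients on a haemodynamic trigger and gives up the randomised comparison

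*Protocol article*

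**What the plan says.** The Analysis groups section puts the primary outcome and the clinical secondary outcomes on an intention-to-treat (ITT) footing, with per-protocol (PP) analyses as supplements. The physiological outcomes are treated differently: "The haemodynamic and biochemical parameters are analysed only in the subgroup that is monitored with advanced haemodynamic monitoring according to the PP principle". The patients left out are "subjects with a spinal anaesthetic without adequate preoperative spread, and/or where lidocaine infusion was prematurely terminated, and/or where the surgery was converted" to an open operation. No as-randomised analysis of these parameters is stated.

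Interventions and measurements gives the grounds for ending lidocaine early: "The infusion is terminated at the end of surgery or earlier in the event of unexplained severe hypotension or severe arrhythmias". The Ethics section repeats them: "The infusion is stopped prematurely if severe unexplained hypotension or arrhythmia occurs".

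The subgroup is described as follows: "In a subgroup of 50 patients having surgery at US Linköping, additional haemodynamic measurements will be performed". What is recorded there includes "Mean arterial pressure, cardiac index, stroke volume index, heart rate, stroke volume variation, pulse pressure variation, systemic vascular resistance index". Table 2 lists the advanced-monitoring variables as outcomes 33–41 and the inflammatory markers as outcome 42.

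**The concern.** Whether a lidocaine infusion runs to the end of surgery is known only after randomisation, and only in the lidocaine arm. The two reasons given for stopping it are circulatory. Dropping these patients therefore removes lidocaine patients because of the kind of measurement the subgroup exists to compare. Nothing in the spinal arm matches this: a spinal patient with equally severe hypotension stays in.

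The spinal arm has its own exclusion, inadequate spread. The Introduction attributes low blood pressure under a morphine spinal to sympathetic block, so these are plausibly the patients with the least block. Conversion to open surgery is a third post-randomisation exclusion, but it applies to both arms.

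For the haemodynamic indices the risk is a difference partly produced by selection. For the inflammatory markers the selection is indirect, and the main problem is that the groups compared are no longer those formed by randomisation. The Introduction says knowledge of blood pressure management in these patients should guide physiologically sound treatment, so a distorted contrast would matter in practice.

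**Working it through.** **The plan's own figure.** The only computed figure is the primary sample size. With a difference of 8 and variance 400, n = 2 × (1.960 + 0.842)² × 400 / 8² ≈ 98.1, or 99 per group. The t-test solution is 99.08, rounded up to the stated 100. It reproduces but does not bear on this point. The article gives no calculation for the subgroup.

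**Inputs from the document.** The subgroup has 50 patients. Allocation uses "opaque and sealed envelopes in series of 20 with both groups distributed 1:1", so about 25 per arm. Tests are two-sided at 0.05.

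**Assumptions.** The document gives no early-termination rate and no link between the stopping trigger and any measured variable. Let f be the share of lidocaine patients dropped and ρ the correlation between trigger and outcome. The outcome is standard normal with no true difference between arms.

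**Formula.** Dropping the adverse tail of the trigger in one arm shifts that arm's mean by

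bias = ρ × φ(z_f) / (1 − f).

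- f = 4% (1 of 25), ρ = 1: z = −1.751, φ = 0.0862, bias = 0.0862 / 0.96 = 0.090 SD.
- f = 20% (5 of 25), ρ = 1: z = −0.842, φ = 0.2800, bias = 0.2800 / 0.80 = 0.350 SD.

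Type I error comes from 20,000 simulated trials per scenario, using a pooled t-test on one value per patient. This simplifies the mixed models planned for longitudinal haemodynamics.

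| Lidocaine patients dropped | Bias, ρ = 1 | Type I error, ρ = 1 | Bias, ρ = 0.5 | Type I error, ρ = 0.5 |
|---|---|---|---|---|
| 2% | 0.049 SD | 0.051 | 0.025 SD | 0.051 |
| 4% (1 of 25) | 0.090 SD | 0.060 | 0.045 SD | 0.051 |
| 8% (2 of 25) | 0.162 SD | 0.086 | 0.081 SD | 0.057 |
| 12% (3 of 25) | 0.227 SD | 0.123 | 0.114 SD | 0.068 |
| 20% (5 of 25) | 0.350 SD | 0.226 | 0.175 SD | 0.086 |

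With everyone kept as randomised, the bias is zero and the simulated type I error was 0.047 to 0.051.

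**Scale.** The standard error of a difference with 25 per arm is √(2/25) = 0.283 SD. One patient dropped therefore biases the result by at most about a third of a standard error (0.090 / 0.283). Five dropped under perfect selection exceeds one standard error (0.350 / 0.283 = 1.24).

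**Both arms.** If the spinal arm also lost the same share from the opposite tail, the bias would double. At f = 8% and ρ = 1 it would be 0.323 SD with type I error 0.219. This needs a further assumption, that inadequate spread picks out the opposite extreme of the same variable.

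**The case against.** The best defence is that the subgroup asks a mechanistic question. The Introduction is interested in low blood pressure in patients who have a working morphine spinal, and leaving out failed blocks fits that. The PP label is open and prespecified. This stands as a reason to keep a PP analysis. It does not justify PP as the only comparison of randomised arms, and it does little to defend the lidocaine exclusion.

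The effect may also be small. Stopping requires a severe event, and severe arrhythmia and advanced heart failure are exclusion criteria at entry. This stands: the size is unknown and could be negligible.

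A separate analysis plan might add an ITT analysis. But the article fixes PP for these parameters while spelling out ITT with supplementary PP for the others, so this is a stated choice and not a detail left open.

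Four stronger readings are tempting, and the document does not support them.

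- A reader might infer that no ITT analysis covers blood pressure. The text does not say whether outcomes 26–32 (hypotensive time, MAP extremes, norepinephrine) count as clinical secondary outcomes (ITT, all patients) or as haemodynamic parameters (PP, subgroup). Supplemental table 1 is not shown. The point is certain only for outcomes 33–42.
- A reader might infer that lidocaine safety data are distorted. The Discussion's remark on safety data concerns the whole study, and premature stopping is counted as outcome 9 and in Box 1.
- A reader might infer that the lidocaine and spinal exclusions push every outcome the same way. That is plausible for blood pressure but not shown for contractility, stroke volume or pulse pressure variation, arterial elastance or the biomarkers. Stopping for arrhythmia need not remove patients with low pressure.
- A reader might take the doubled, two-arm bias as the expected size. It is an upper bound.

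**Conclusion.** The concern holds for outcomes 33–42. The stated analysis set excludes patients after randomisation, by arm-specific rules. On the plan's own account of why lidocaine is stopped, one of these rules selects directly on haemodynamics.

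The direction and size are not established. The range of about 0.05 to 0.35 SD covers lidocaine exclusions of 1 to 5 patients out of 25. It rests on assumed rates, assumed correlations and a normal outcome, and its top end requires perfect selection. For comparison, 25 per arm has 80% power only for differences of about 0.81 SD, so even the top end is less than half of what the subgroup could reliably detect (0.35 / 0.81 = 0.43).

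These are secondary outcomes in a single-site subgroup. The primary analysis is untouched. The change is still worth making because it is cheap and restores the randomised comparison.

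**What to change.** In the Analysis groups section, or in the analysis plan if one is still open:

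- Make the main analysis of outcomes 33–42 as randomised, in all subgroup patients with measurements, including values recorded after the infusion was stopped or the surgery converted.
- Keep the PP set as a supplementary mechanistic analysis, as is already done for the primary outcome.
- Report the number excluded from the PP set by arm and by reason.
- State that the blood pressure and norepinephrine outcomes (26–32) are analysed by ITT.

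The cost is a few sentences. No new measurements are needed, since monitoring data are stored continuously and manual readings are scheduled up to PACU discharge. With 54 patients included by 1 October 2025 and recruitment expected to run to the end of 2027, the change can be fixed before the randomisation code is broken. The downside is slight dilution of the mechanistic contrast, which the retained PP analysis still shows. No clinical rule changes.
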